### Enhanced screening vs standard screening conditions

The “enhanced” screening condition is implemented in 25 of our 50 PHC catchment areas, allowing us to examine whether the added community-based screening through community health fairs a) increases identification of patients with co-morbid diagnosis (Table 1); and b) improves linkage to and retention in care, compared to co-morbid patients identified via standard PHC-based screening. Specific recruitment procedures for each setting are described below, followed by common screening procedures and tests.

**Table 1 Tab1:** Initial and Confirmatory Screening Criteria

Screening stage	Inclusion criteria at each stage
Initial Screening Inclusion Criteria *Enhanced screening (health fair or PHC)* *Standard screening (PHC only)*	*Age:* 30 years or older *Mental competency:* Modified Short Blessed Cognitive Test [103] score ≤7 *General psychological distress*: The Kessler-10 [81] score ≥6 *One or more of the following cut-off measures for diabetes, hypertension, and/or CVD:* • Capillary Blood Sugar ≥160 mg/dL • Blood pressure ≥ 140/90 mmHg • Possible Angina: Rose angina questionnaire [104]^a^ • Self-reported physician-diagnosed history of DM, hypertension or ischemic heart disease
Confirmatory Screening Inclusion Criteria (PHC only)	*Depression/anxiety*: The Mini-International Neuropsychiatric Interview (MINI) [82] *One or more of the following clinical measures for diabetes, hypertension, and/or CVD:* • Blood pressure ≥ 140/90 mmHg • Capillary blood sugar ≥160 mg/dL • Physician-diagnosed history of DM, hypertension or ischemic heart disease (patient must show prescription or medication) • Possible rose angina^b^
Exclusion Criteria	• not mentally competent to provide consent per the standard screener [103], answer to study measures and/or participate in the intervention. • Participants who do not provide contact information

^a^ Patients who screen negative for hypertension and DM, but have possible angina on the rose angina questionnaire will be invited to the confirmatory screening

^b^ Patients who screen positive on the rose angina measure at initial screening and positive on the MINI during the confirmatory screening, but negative on hypertension and DM are marked as tentatively enrolled on the confirmatory screening form. At the baseline assessment electrocardiogram and cholesterol to check for CVD will confirm eligibility

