#### Screening

To test the hypothesis that, compared to standard screening, enhanced screening will result, on an average, in more people being identified as co-morbid for CMD and CVD/DM during the confirmatory testing at the PHC, we will use a Poisson regression model - or in case of over dispersion, a negative binomial model - with PHC as the unit of analysis, and population size in the catchment area of the PHC included as an offset.

Secondary analysis will explore subsequent linkage and retention in care of enrolled participants first screened at the community health fairs compared to those first screened at PHC. These participants will be compared by examining the proportion of participants who started treatment both by the 6 week follow-up, as well as the proportion retained throughout the study. We will use a mixed-effects logistic regression model with a random intercept for PHC.

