#### Intervention

The primary, intention-to-treat (ITT) analyses will evaluate the impact of the intervention, both in terms of a) return to below-threshold levels for CMD and CVD/DM risk (i.e. dichotomized outcomes), and b) improvement in the levels of the continuous CMD and CVD/DM measures (depression and anxiety scores, BP, HbA1c, LDL, and serum creatinine levels) via logistic and linear mixed-effects regression models respectively, with repeated measures nested within individuals, and individuals nested within PHC, and random intercepts for individuals and PHC [96, 97]. The trajectories of the continuous variables will be examined via the time-by-intervention interaction effect. We will run separate regressions for the various outcomes, to allow us to detect if different variables react to the intervention at different rates. To prevent Type I error inflation, we will lower α accordingly. In all models covariates will be included as necessary.

The sample size of 1250 in each intervention arm (50 participants per PHC), was determined based on achieving 80% power for the ITT analyses regarding the effect of the intervention, and was calculated as follows: we assumed an attrition rate of 20%, and an intra-class correlation (ICC) of 0.1 to account for clustering of participants in PHCs, which reduces the initial sample size to an effective sample size of *n* = 204/group. Pooling data across the three post-intervention measurements triples this number, and subsequent adjustment for repeated measures with an assumed ICC = 0.5, results in a final *effective* sample size of *n* = 306 person-time observations per group. Based on previous research, we assumed 40% of control group participants to recover [98, 99]. With α = .025, the minimum detectable effect size at 80% power is 12% more of the intervention group participants recovering [100]. This is a small effect size according to Cohen [101], and comparable to earlier studies in the US [26]. To test the screening hypothesis, with 25 PHCs per screening condition, 80% power and α = 0.05, the minimum detectable effect in a Poisson regression is 2.1 times as many co-morbid cases identified with the enhanced compared to the standard screening [102]. Although this is a large effect, we deemed it attainable, given the documented under-reporting of mental health in standard care [10, 11], and the intensive nature of our enhanced screening.

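### The screening test's detectable ratio of 2.1 fits a Poisson model only at about one confirmed case per PHC, whereas the same paragraph plans 50 enrolled per PHC

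*Protocol article*

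**What the plan says.** The power statement for the screening hypothesis closes the sample size paragraph of the protocol article (Statistical analyses, Intervention). Its inputs are "To test the screening hypothesis, with 25 PHCs per screening condition, 80% power and α = 0.05", and its result is that "the minimum detectable effect in a Poisson regression is 2.1 times as many co-morbid cases identified with the enhanced compared to the standard screening". The paragraph calls this a large effect and defends it as attainable. It gives no expected number of cases per PHC and no allowance for variation between PHCs.

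The same paragraph opens with the recruitment target: "The sample size of 1250 in each intervention arm (50 participants per PHC").

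The planned analysis (Statistical analyses, Screening) models the number of people found co-morbid at confirmatory testing. It uses a Poisson regression, "or in case of over dispersion, a negative binomial model", with the PHC as the unit and catchment population as the offset. No dispersion value is given there either.

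**The concern.** The number of PHCs alone does not fix the detectable ratio in a Poisson comparison. What matters is the total number of events, that is, PHCs multiplied by expected cases per PHC. A ratio as large as 2.1 from 25 PHCs per arm implies very few events, while the recruitment plan implies many.

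The stake is the reading of Aim 1. A reader who takes 2.1 at face value will think the screening comparison can detect only a doubling, whereas its sensitivity could be anywhere from very good to about that poor, depending on how much PHCs differ. The printed figure hides the quantity that decides this, the between-PHC variation.

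**Working it through.** **Inputs from the protocol article**

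- PHCs per screening arm: 25 and 25. Power 80%, α = 0.05 (Statistical analyses, Intervention). Sidedness is not stated; I take two-sided and comment on one-sided below.
- Stated ratio: 2.1 (same paragraph).
- Count analysed: people confirmed co-morbid at the PHC (Statistical analyses, Screening).
- Enrolment: 50 per PHC (Intervention). Only patients who pass confirmatory screening are invited (Enhanced screening vs standard screening conditions). Both screening arms are divided between the two care arms (Setting and randomization), so standard-screening PHCs must also supply 50.
- Catchment: 30,000 per PHC as stated (Setting and randomization), so exposure is taken as equal.

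**Step 1. What count makes 2.1 right under Poisson?**

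Let λ be the mean count per standard-screening PHC and RR the ratio. The Wald condition is

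(1.96 + 0.842)² × (1/25) × (1/λ)(1 + 1/RR) = (ln RR)²

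With RR = 2.1: ln 2.1 = 0.742, squared 0.550; (1.96 + 0.842)² = 7.85; 1 + 1/2.1 = 1.476.

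λ = 7.85 × 1.476 / (25 × 0.550) = **0.84 cases per PHC**

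If the null variance is used in the α term, as in a common Poisson-regression formula:

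λ = [1.96 × √4 + 0.842 × √(2 + 2/2.1)]² / (50 × 0.550) = **about 1.05**

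Pooled-null, rate-difference and square-root versions, one-sided 0.05 and two-sided 0.025 all stay between about 0.6 and 1.3. With exactly one case per PHC the null-variance formula returns 2.13. So 2.1 can be reproduced, but only at about one case per PHC.

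**Step 2. What count does the plan imply?**

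The enrolled are a subset of the confirmed, apart from a few tentative enrolments on the angina questionnaire pending baseline tests (Table 1, note b). Fifty enrolled therefore implies roughly 50 or more confirmed cases per PHC. The other results in the paragraph do rest on this 50: 1250 × 0.8 = 1000, 1000 / (1 + 39 × 0.1) = 204, and 204 × 3 / (1 + 2 × 0.5) = 306.

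**Step 3. Poisson detectable ratio at realistic counts (Wald, two-sided 0.05)**

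| Mean per standard PHC | Detectable ratio |
|---|---|
| 5 | 1.39 |
| 10 | 1.27 |
| 23.8 (= 50/2.1) | 1.17 |
| 50 | 1.115, i.e. about 1.12 |
| 100 | 1.08 |

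At 50 per PHC, power for a ratio of 1.12 is 83% by formula and 83% by simulation.

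**Step 4. Add variation between PHCs**

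The article gives no CV, so the range below is an assumption. With

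Var(ln RR) = [(1/λ + CV²) + (1/(RR·λ) + CV²)] / 25

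and λ = 50:

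| Between-PHC CV (assumed) | 0 | 0.25 | 0.5 | 0.75 | 1.0 |
|---|---|---|---|---|---|
| Detectable ratio | 1.12 | 1.25 | 1.51 | 1.83 | 2.22 |

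**Step 5. What CV would give 2.1 at 50 per PHC?**

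CV² = [25 × 0.550 / 7.85 − (1/50)(1.476)] / 2 = (1.753 − 0.030) / 2 = 0.862, so CV = **0.93**. At a mean of 50 the variance would be 1 + 50 × 0.862 = about 44 times the mean.

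**The case against.** The best defence is that 2.1 is not absurd. The analysis section foresees over-dispersion, and 2.1 falls within the range in Step 4. The article cites a reference for the calculation and is a condensed account, so the base count and dispersion may be recorded elsewhere. This stands in part: 2.1 may prove close to the truth if PHCs differ very widely. But the text attributes the figure to a Poisson regression, and under that model no count near the plan gives it. It could be defended only with another model and an unstated, very large CV.

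A second defence is that nothing hangs on the figure. The sample size was set by the intervention comparison, the regression estimate and its p-value do not depend on the detectable ratio, and under Poisson the error is on the safe side. This stands, and it limits the weight of the point.

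Two stronger readings may tempt a reader, and the article supports neither:

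- *A 2.1-fold effect cannot coexist with 50 per PHC in both arms.* This confuses confirmed with enrolled counts. Confirmed patients are invited, not automatically enrolled; 50 against 105 confirmed, with 50 enrolled in each, is a ratio of 2.1.
- *Shared screening tools undo the argument that 2.1 is attainable.* The two conditions do have "followed by common screening procedures and tests", and under-reporting in standard care is one stated reason. But the paragraph also relies on the intensity of the enhanced screening, which includes outreach, home visits and weekly fairs. Common instruments at the PHC do not reach people who never attend, whereas fairs may.

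**Conclusion.** The figure of 2.1 is wrong for the model and design beside which it is printed. Under Poisson it needs about one confirmed case per standard-screening PHC; the plan implies roughly 50 or more, where the value is about 1.12 (1.17 at about 24). This rests on equal exposure, a two-sided test and the enrolled being essentially a subset of the confirmed; reasonable changes to the formula, sidedness or α do not alter it.

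Two further inferences should be resisted. The error does not show Aim 1 to be underpowered: under Poisson the stated ratio is conservative. Nor is 1.12 the trial's true sensitivity, because variation between PHCs will raise it by an amount that the article gives no basis for fixing. For a true ratio of 1.5 at 50 per PHC, power is above 99% with a CV of 0.25 and 79% with 0.5. The article does not say that a result below 2.1 would be dismissed; the harm is that readers are misinformed about what the comparison can detect.

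**What to change.** Replace 2.1 with the detectable ratio at the planned count, allowing for over-dispersion, and show it over an assumed CV range such as 1.12, 1.25, 1.51, 1.83 and 2.22 for CVs of 0, 0.25, 0.5, 0.75 and 1.0 at 50 per PHC. State the count and dispersion used. If 2.1 did come from an over-dispersed calculation, name that model and its inputs instead of a Poisson regression.

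Make explicit that the Aim 1 count includes every confirmed case, not only those enrolled up to 50 per PHC. A count capped by enrolment would pull the ratio towards 1 whatever the screening effect.

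The existing plan to move to a negative binomial model if over-dispersion appears can stay; using it from the outset is a modelling preference. The cost is one recalculation and a few sentences in the analysis plan. It needs no new data beyond the screening log and no change to the sample size.

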#### Current status of the study

Intervention and assessments are ongoing as of August 3, 2018. During the final year of our research, a dissemination meeting will be held for key stakeholders including local, state, and national government officials, and hospital administration officials.

## Discussion

This randomized controlled trial evaluates the effectiveness of multi-level integrated clinic and community-based intervention model for common mental disorders co-morbid with diabetes and cardiovascular conditions compared to enhanced care as usual. In addition, we test the effectiveness of using ASHAs as link workers between the community and the PHC in increasing referrals of such patients to the clinic and improving retention rate in the treatment regimen. A novel feature of this proposal includes group sessions that target risk behaviors common to both depression and co-morbid medical conditions. Our intervention builds on collaborative care model and is dependent on trained PHC physicians to deliver evidence based intervention for both CMD and co-morbid medical conditions and directly addresses the scarcity of trained mental health professionals in rural India. It has a high potential for scale up and sustainability as it builds on strengthening the linkages between the community and the existing Government programs.

## Abbreviations

ASHA: Accredited social health activist
BMI: Body mass index
BP: Blood pressure
CAD: Coronary artery disease
CMD: Common mental disorder
CVD: Cardiovascular disease
DM: Diabetes mellitus
GAD: Generalized anxiety disorder
ITT: Intention to treat
MINI: Mini international neuropsychiatric interview
PHC: Primary health center
PHQ: Patient health questionnaire
RCT: Randomized controlled trial
WHO: World Health Organization
